#### Statistical analysis

2.4.2

A detailed Statistical Analysis Plan (SAP) will be prepared before the final analysis. Simple summary statistics will be generated for baseline characteristics (demographics, somatometric parameters, comorbidities, and type of injuries) and outcomes recorded at scheduled FU assessments. Categorical variables will be summarized using frequency and percentage for each category; continuous variables will be summarized using mean, standard deviation, median, interquartile range, and minimum and maximum values. Continuous variables with both baseline and FU measurements available will also be summarized as changes between baseline and FUs at the individual patient level.

AEs will be reported both at patient level and AE level. The risk estimates will be presented along with the 95% Clopper-Pearson confidence interval. When calculating the AE rates, the denominator will be the full analysis population, irrespective of dropouts during FU. Sensitivity analyses will be conducted excluding patients who dropped out of the study and had not experienced an AE. For patients treated with Clavicle Plates, the risk of experiencing any ADE within 24 months after surgery will be reported. For the calculation of the ADE rate, only ADEs with onset before or within the upper visit window of the 24 months visit will be included. For patients treated with Clavicle Hook Plates, the risk of experiencing any ADE between surgical treatment and 12 months after removal of the Clavicle Hook Plate will be reported. Separate sub analyses on the risk of experiencing an ADE between surgery and Clavicle Hook Plate removal and within 12 months after the Clavicle Hook Plate removal will be performed. Separate ADE rates for the two FU periods including only ADEs with onset within the upper boundary of the visit window of the corresponding FU period will be calculated. For incidences of complaints related to plate prominence or discomfort and to local pain, incidence rates will be calculated, and summary statistics presented, including the number and percentage of patients with complaints related to plate prominence or discomfort (defined as NRS ≥1) and local pain (defined as NRS ≥3). For the reoperation rate due to ADE, fracture union rate, rate of stable AC joint healing at one-year post-removal, the full analysis population will be used as the denominator. Descriptive analyses on the rate of implants removed and the reasons for implant removal will be conducted. Simple summary statistics (i.e., numbers and percentages) will be produced for each bone healing category. QuickDASH, will be measured repeatedly during the FU period and analyzed using mixed effects models for repeated measures (MMRM). PROs also measured repeatedly during the FU period will likewise be analyzed using MMRM. For the surgeons' evaluation, simple summary statistics including numbers and percentages will be produced for each category.

An interim analysis will be performed as soon as 30 patients in each group have reached the timepoint of 6 months after surgery. The main purpose of the analysis is to ensure safety, while the potential implications could include stopping the study, amending the protocol, or early dissemination of results, depending on the analysis of the study. Definition of the analysis populations will be specified in the SAP.

The planned statistical analysis will allow for repeated analyses on the per-protocol population in cases of major protocol deviations, as well as sensitivity analyses excluding patients who dropped out of the study and had not experienced an AE. Some degree of missing data is expected. Patients may withdraw from the study prior to completion of the intended FU for reasons such as death, severe intercurrent illness, withdrawal of consent, and loss to follow-up. In case of missing data a decision will be made whether special analysis methods are required to handle missing data on an individual basis for each endpoint (as defined in the SAP). This decision will be made based on the extent of the missing data and the likelihood of bias occurring because of the missing data, and the importance of the endpoint. Protocol deviations will be collected in the study database in a specific protocol deviation form and listed in the final analysis. All protocol deviations will be reviewed during the data review meeting prior to final analysis.

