#### Termination of participation

2.3.6

Patient participation in the study may terminate for reasons such as withdrawal of informed consent, failure to commence treatment within the study, post enrolment screening failure, investigator's discretion (e.g., patient noncompliance), loss to FU, death, and other unspecified reasons. Detailed information explaining the reasons for termination will be recorded in a dropout form. For these patients, the collected data will be censored at the day of termination and may be used in the analysis.

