#### Sample size determination

2.4.1

The study objective is to describe long term outcomes (status following healing of the related clavicle injuries) in a minimum of 30 patients with shaft fractures treated with Clavicle Plates and 30 patients with lateral fractures/AC dislocations treated with Clavicle Hook Plates. Assuming a 20% dropout rate at two years, the study will need to enroll 76 patients (38 patients per group).

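### ADE and ADE-related reoperation risks count dropouts as event-free, which biases them low, and the planned sensitivity analysis does not reliably bound the truth

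*Protocol article*

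**What the plan says.** Section 2.4.2 of the protocol article (Statistical analysis) says of AE rates that "the denominator will be the full analysis population, irrespective of dropouts during FU". On precision it says: "The risk estimates will be presented along with the 95% Clopper-Pearson confidence interval".

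The quantities to be reported are risks over a period. For Clavicle Plates, "the risk of experiencing any ADE within 24 months after surgery will be reported", and for the numerator "only ADEs with onset before or within the upper visit window of the 24 months visit will be included". For Clavicle Hook Plates, "the risk of experiencing any ADE between surgical treatment and 12 months after removal of the Clavicle Hook Plate will be reported", with separate sub-analyses for the time up to removal and for the 12 months after it. The full analysis population is also named as the denominator for the rate of reoperation due to an ADE.

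On dropout, the same section states: "Sensitivity analyses will be conducted excluding patients who dropped out of the study and had not experienced an AE". Section 2.3.6 (Termination of participation) says that, for patients who leave, "the collected data will be censored at the day of termination and may be used in the analysis". Section 2.4.1 plans for 20% dropout at two years. Section 2.4.2 also leaves open, endpoint by endpoint, whether special missing-data methods will be needed, and it defers the analysis populations to the SAP.

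**The concern.** A 24-month risk describes patients followed for 24 months. If a patient lost at week 6 without an ADE stays in the denominator, no later event can reach the numerator, and the patient counts as event-free to the end. The sensitivity analysis makes the opposite choice, and there a dropout is kept or removed according to whether an event was seen. Neither calculation uses the date on which follow-up ended.

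Safety heads the list of objectives. The article presents the study as early evidence on a new system and expects it to inform later comparative studies. In a descriptive study the point estimate is the result. An ADE or reoperation risk that is systematically low favours the device and would be carried forward as a benchmark.

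**Working it through.** **1. Inputs.** From the plan: 30 evaluable patients per group, 20% dropout at two years, 38 enrolled per group, and the two denominators above. Assumed, because the documents give no figure: the true ADE risk R (5% to 50%), dropout unrelated to ADE risk and spread evenly in rate over 24 months, and a constant ADE hazard unless stated otherwise. The AE-rate rules are applied to the ADE risk, which is their natural reading.

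**2. The plan's own figure.** 30 / (1 − 0.20) = 37.5, rounded up to 38 per group, and 2 × 38 = 76. This matches. Expected dropouts are 0.20 × 38 = 7.6, about 8 per group.

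**3. Expected value of each estimate.** Let λ = −ln(1 − R)/24 and δ = −ln(0.80)/24.

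- Full population: M = λ/(λ+δ) × (1 − e^(−24(λ+δ))), the share whose ADE is seen before any dropout.
- Event-free dropouts deleted: S = M / (M + e^(−24(λ+δ))), since only patients with an event and event-free completers remain.

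For R = 20%: λ = δ and e^(−24(λ+δ)) = 0.8 × 0.8 = 0.64. So M = 0.5 × 0.36 = 18.0% and S = 0.180/0.820 = 22.0%.

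For R = 30%: 24λ = 0.3567, 24δ = 0.2231 and e^(−24(λ+δ)) = 0.7 × 0.8 = 0.56. So M = (0.3567/0.5798) × 0.44 = 27.1% and S = 0.271/0.831 = 32.6%.

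In patients, the shortfall is 38 × 0.020 = 0.8 and 38 × 0.029 = 1.1.

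| True risk | Full population | Event-free dropouts deleted | 1 − Kaplan-Meier (simulated mean, n = 38) |
|---|---|---|---|
| 10% | 9.0% | 11.1% | 10.0% |
| 20% | 18.0% | 22.0% | 20.0% |
| 30% | 27.1% | 32.6% | 30.0% |
| 50% | 45.4% | 53.2% | 50.0% |

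**4. Other hazard shapes and dropout levels.** For a true 20%, front-loaded ADEs (Weibull shape 0.5) give 18.7% and 22.6%; back-loaded ADEs (shape 2) give 17.3% and 21.3%. Over true risks of 5% to 50% and all three shapes, with 20% dropout, the full-population figure is low by 0.3 to 6.4 points and the other is high by 0.4 to 4.1 points. With dropout between 10% and 30%, these ranges become 0.2 to 9.8 and 0.2 to 6.5 points.

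**5. Dropout related to device problems.** Take 38 patients, 6 with an ADE and 8 event-free dropouts. The plan would report 6/38 = 15.8% (Clopper-Pearson 6.0% to 31.3%) and 6/30 = 20.0% (7.7% to 38.6%). If the 8 lost patients have residual risk r, the complete-follow-up risk is (6 + 8r)/38:

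- r = 10%: 17.9%
- r = 20%: 20.0%
- r = 30%: 22.1%
- r = 50%: 26.3%

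The sensitivity figure is exact when r equals 6/30. Below that it is too high; above it, both reported figures are too low.

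**6. Interval.** In simulation at n = 38, with true risks from 10% to 50% and 20% dropout, the coverage of both Clopper-Pearson intervals stayed at about 94% to 98%.

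**The case against.** The case for leaving the plan alone is mainly about size. The study is descriptive, with no hypothesis, threshold or comparator resting on this number. The bias is about one patient per group, while the interval for 6/38 spans 25 points. Two figures will be reported, and if dropout is unrelated to ADE risk they do enclose the true value. The SAP may add a censoring-based estimate under the open missing-data clause. All of this stands and limits the weight of the point.

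It does not remove the point. The direction of the error is known and avoidable, the open clause does not alter denominators already stated, and the enclosure fails when patients leave because of the device. Nor is a full denominator conservative here: that holds for union or joint healing, where a lost patient counts as not achieved, but not for harms.

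A reader might infer more than the documents support:

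- *The sensitivity figure is always too high.* Step 5 shows that this depends on the lost patients' residual risk.
- *The confidence intervals fail.* Coverage holds; the distortion is in the point estimate.
- *The bias is much larger because dropout is early.* If all dropout fell at month 1, a true 30% would read 0.8 × 0.30 + 0.2 × (1 − e^(−λ)) = 24.3%, but the plan gives only a two-year total and no timing.
- *Unremoved hook plates dilute the post-removal risk by a known amount.* The article states no denominator for that sub-analysis. Carrying over the general rule is an inference, no non-removal share is given, and Table 3 lists removal surgery as a visit.
- *The ±2-month window at 24 months distorts the risk.* The numerator cut-off is stated openly, and the effect is minor.
- *Sections 2.3.6 and 2.4.2 contradict each other.* Censoring in 2.3.6 may mean only that data stop at termination; it does not promise a time-to-event analysis.

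**Conclusion.** The point holds as a moderate one. As written, the ADE risk for both plate types and the ADE-related reoperation rate understate the complete-follow-up risk unless no dropout would have had a later event. At the planned 20% dropout the shortfall is about 2 points at a true 20% and about 3 points at a true 30%. These sizes rest on an assumed true risk, a constant hazard and dropout unrelated to ADE risk. The direction of the main estimate's bias does not depend on those assumptions. The direction for the sensitivity analysis does, so the two figures cannot be presented as bounds. The post-removal hook-plate risk needs its denominator stated; no size can be given for it from the documents.

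**What to change.** Report the ADE risk and the ADE-related reoperation risk as Kaplan-Meier cumulative incidence, or Aalen-Johansen with death as a competing event if deaths occur. Censor at termination and read the curve at a fixed time with a 95% CI: 24 months from Day 0 for Clavicle Plates. For the combined hook-plate period, name the reading time in advance, because removal dates differ between patients. For the post-removal hook-plate risk, state that the clock starts at Day 0′ and that the denominator is patients whose plate was removed.

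Keep the full-population proportion with its Clopper-Pearson interval as a supportive analysis. The exclusion of event-free dropouts may stay only if it is labelled as outcome-dependent.

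The cost is wording in the SAP, plus a recorded change to the denominators that the protocol article already states. ADE onset and the day of termination are already needed under Sections 2.4.2 and 2.3.6, so no new data and no larger sample are required. The reported risk becomes slightly less favourable. Kaplan-Meier still assumes non-informative censoring, so reasons for dropout should be shown beside the estimate.

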In this study, a prospective, observational design is used which will allow an assessment of the 2.7 mm VA-LCP Clavicle Plates and 2.7 mm Clavicle Hook Plates when they are used per SoC, as the protocol does not influence the clinical decision-making process. MMRM will be used to analyze PROs and QuickDASH, allowing us to consider the within-subject correlations, and adjust for baseline characteristics and other covariates, improving estimate and inference precision. Additional analyses will be adjusted as appropriate, depending on their objectives and model assumptions. The list of confounders and the details of the adjustment methods will be fully specified in the Statistical Analysis Plan. The sensitivity analysis, the analysis restricted to per-protocol population, and the handling of missing data (if deemed necessary) will help assess whether the conclusions remain consistent when accounting for potential biases introduced by major protocol deviations, missing data, and/or patient dropout.

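### The adverse-device-effect and reoperation risks are crude proportions that treat event-free dropouts as followed to the horizon, which biases them low, and the one named dropout check selects on the outcome

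*Protocol article*

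**What the plan says.** Section 2.4.2 (Statistical analysis) of the protocol article fixes how the safety risks are calculated. For adverse event rates, "the denominator will be the full analysis population, irrespective of dropouts during FU". The named targets are the risk of any ADE within 24 months of surgery (Clavicle Plates) and from surgery to 12 months after plate removal (Hook Plates). Separate sub-analyses cover the periods before and after hook plate removal. Intervals are 95% Clopper-Pearson. The full analysis population is also the denominator for a second list of outcomes, which opens "For the reoperation rate due to ADE, fracture union rate" and closes "rate of stable AC joint healing at one-year post-removal, the full analysis population will be used as the denominator".

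One analysis is named for dropout: "Sensitivity analyses will be conducted excluding patients who dropped out of the study and had not experienced an AE". It is named again later in the same section.

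Section 2.3.6 (Termination of participation) says that for patients who leave early "the collected data will be censored at the day of termination and may be used in the analysis". Section 2.4.1 assumes 20% dropout at two years. Section 2.4.2 also leaves the definition of the analysis populations, and any special missing-data methods, to the statistical analysis plan. The Discussion says that the sensitivity, per-protocol and missing-data analyses together "will help assess whether the conclusions remain consistent when accounting for potential biases" from deviations, missing data and dropout.

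**The concern.** A risk up to a fixed time needs every patient observed to that time, or a method that allows for those who were not. A crude proportion does neither. A plate patient lost at month 3 with no ADE adds one to the denominator for all 24 months and can add nothing to the numerator after month 3. Later events in dropouts are missed and none can be added, so on average the reported risk cannot exceed the true one, whatever the reason for dropout. For a safety endpoint the error favours the device.

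The sensitivity analysis does not repair this. A dropout stays in if an event was recorded and leaves if not, so inclusion depends on the outcome. It also selects on any adverse event while the quantity reported is ADE.

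Safety is the first objective in section 2.2, and the Discussion expects these results to inform later comparative studies. A rate that is too low would carry over into their design.

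**Working it through.** **The plan's own figure.** 30 evaluable patients per group with 20% dropout: 30 / (1 - 0.20) = 37.5, rounded up to 38; 2 × 38 = 76. This reproduces section 2.4.1.

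**Inputs.** From the article: 38 patients per group and dropout d = 0.20. Assumed, because the article gives no figure: true 24-month risk R; dropout independent of ADE; dropout times uniform over months 0-24 or 3-12; ADE hazard front-loaded, constant or rising (Weibull shape k = 0.5, 1 or 2).

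**Formulas.** Risk by month t: F(t) = 1 - (1 - R)^((t/24)^k). Let m be the average of F(t) over the dropout times, that is, the chance that a dropout has an ADE before leaving.

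- Planned rate: p = (1 - d) × R + d × m
- Sensitivity analysis: s = p / [p + (1 - d) × (1 - R)]

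The formula for s treats adverse event and ADE as the same.

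**One case in full.** R = 0.30, constant hazard, uniform dropout over 0-24 months: m = 0.159. Then p = 0.8 × 0.30 + 0.2 × 0.159 = 0.272, and s = 0.272 / (0.272 + 0.56) = 0.327.

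**All cases at a true 30%:**

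| ADE hazard | Dropout months | m | Planned rate | Sensitivity analysis |
|---|---|---|---|---|
| Front-loaded | 0-24 | 0.209 | 28.2% | 33.5% |
| Front-loaded | 3-12 | 0.178 | 27.6% | 33.0% |
| Constant | 0-24 | 0.159 | 27.2% | 32.7% |
| Constant | 3-12 | 0.105 | 26.1% | 31.8% |
| Rising | 0-24 | 0.107 | 26.1% | 31.8% |
| Rising | 3-12 | 0.038 | 24.8% | 30.7% |

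In the extreme case of all dropout at time 0, m = 0, the planned rate is 0.8 × 30% = 24.0%, and the sensitivity analysis gives 0.24 / (0.24 + 0.56) = 30.0%, which is unbiased.

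**A censoring-aware comparator.** Simulation with 38 patients, 20% dropout at a constant rate, constant ADE hazard and a true 30% gave average estimates of 27.1% (planned), 32.6% (sensitivity) and 30.0% (Kaplan-Meier). At a true 20% they were 18.0%, 22.0% and 20.0%.

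**Effect on the interval.** The number of patients with a recorded ADE is binomial with n = 38 and probability p. At a true 30%, over the six cases in the table, the Clopper-Pearson interval covers the truth in 93.4-96.7% of trials. Its upper limit falls below the truth in 2.4-6.5%, against 1.4% with complete follow-up (p = 0.30).

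**When the check stops being too high.** Take R = 20% (if dropouts were like completers), constant hazard and all dropout at month 12. Then m = 1 - 0.8^0.5 = 0.106, p = 0.16 + 0.2 × 0.106 = 0.181 and s = 0.181 / (0.181 + 0.64) = 0.221. If dropouts have h times the completers' hazard after month 12, the true risk is 0.16 + 0.2 × [1 - 0.8^(0.5 + 0.5h)]. This equals 0.221 at h of about 2.2. Above that, both planned figures are too low.

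**The case against.** **Left to the statistical analysis plan.** Section 2.4.2 leaves special missing-data methods to that plan, endpoint by endpoint, and the analysis populations too. This stands for methods not yet named. It does not undo the denominator and the sensitivity analysis, which the article itself fixes.

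**Small beside the uncertainty.** There is no formal hypothesis. With 8 events the interval for 8/38 = 21.1% runs from 9.6% to 37.3%, while the bias at a true 30% is about 2 to 5 points. Small numbers and loss to follow-up are disclosed as limitations. All of this stands and lowers the severity. The error is still one-directional and avoidable.

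**The two figures bracket the truth.** They do in the table above, but not if dropouts have a much higher later risk, and they are not presented as bounds.

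Some stronger readings are tempting but not supported:

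- *Every dropout is counted as event-free.* No. A dropout with an ADE recorded before leaving counts as an event.
- *The interval should rest on 30 patients, not 38.* With no events the upper limit would be 11.6% for 0/30 against 9.3% for 0/38, but that assumes that dropouts contribute no follow-up at all.
- *Sections 2.3.6 and 2.4.2 flatly contradict each other.* Censoring at termination may mean only that no later data are used.
- *The Discussion claims that dropout bias is removed.* It says only that several analyses will help to assess consistency.
- *Selecting on adverse events instead of ADEs is a large gap.* Section 2.3.7.1 confines the safety assessment to events related to the device or the procedure, so it is chiefly procedure-only events that separate the two.
- *Union and joint healing are flattered too.* With that denominator, dropouts with no recorded success count as failures, which is conservative.

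**Conclusion.** The point holds for the ADE risks and the reoperation rate due to ADE. The planned rate is biased low under any dropout mechanism that leaves follow-up incomplete. With 20% dropout independent of ADE and spread over follow-up, a true 30% is reported as about 25-28%. The named check is biased high under the same assumptions, at about 31-33%, and that direction does depend on them. Neither figure estimates the risk that section 2.4.2 names.

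The sizes rest on assumed ADE risk and timing and were worked out for the 24-month plate horizon only. For Hook Plates the direction carries over, but the horizon differs between patients and the size was not calculated. This should be fixed, but it does not threaten the study: the analysis is descriptive and interval coverage at a true 30% stays close to nominal.

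**What to change.** In section 2.4.2 and the statistical analysis plan:

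1. **Clavicle Plates.** Estimate the ADE risk and the reoperation-due-to-ADE risk as cumulative incidence at 24 months (Kaplan-Meier, or Aalen-Johansen with death as a competing event), censoring at termination in line with section 2.3.6.
2. **Hook Plates.** A single Kaplan-Meier time point is undefined here, because the horizon depends on each patient's removal date. Use the two periods already defined: one clock from surgery, with removal ending the period, and one from removal, giving a 12-month risk. Combine them, or show the crude overall rate labelled as a lower figure.
3. **Intervals.** Use a log-log interval when there are events. With none, its variance is zero and it is undefined, so use an exact-type interval.
4. **Crude rate.** Keep the full-population proportion, labelled as a lower figure.
5. **Sensitivity analysis.** Replace the outcome-selected exclusion with bounds: dropouts without an ADE all event-free, then all with an event. With 8 ADE patients and 8 event-free dropouts these are 8/38 = 21.1% and 16/38 = 42.1%.
6. **Wording.** Say in section 2.3.6 that data up to termination will be used, and align the Discussion.

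The cost is wording and standard procedures. The onset rule in section 2.4.2 already requires ADE onset dates, and section 2.3.6 already sets censoring at the day of termination. The reported risk will be slightly higher and its interval slightly wider, and the bounds may be wide.

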#### Inclusion criteria

2.3.1

▪Patients aged ≥18 years▪Unilateral clavicle injuries are considered for inclusion in the study. The patient must be undergoing primary surgical treatment within 21 days of injury using either of the following devices according to the manufacturer's instructions for use:
○2.7 mm VA-LCP® Clavicle Plates are used for fixation of clavicle bone fragments. Hereinafter referred to as Clavicle Plates○2.7 mm VA-LCP® Clavicle Hook Plates are used for fixation of lateral clavicle fractures and dislocations of the acromioclavicular joint. Hereinafter referred to as Clavicle Hook Plates▪Expected ability to attend postoperative follow up (FU) visits▪Ability to provide informed consent

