##### Clinical performance

2.3.7.2

Outcome measures related to clinical performance to be recorded are a subset of safety-related parameters including:
▪Incidence of complaints related to plate prominence or discomfort▪Incidence of complaints related to local pain▪Reoperation rate due to AE probably or possibly related to the investigational device▪Fracture union rate▪Rate of stable AC joint healing (if applicable) at one-year post-removal, clinically assessed

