##### Bone and joint healing

2.3.7.3

Bone healing and AC joint healing (in case of Clavicle Hook Plates only) will be assessed by the treating surgeon following local SoC. The global clinical assessment of the patient's status according to the surgeon's judgement will be documented as not assessable, no signs of healing, healing in progress (normal but slow), healing in progress (normal) or healed. In patients receiving Clavicle Hook Plates, the AC joint healing status will be assessed only after the plate has been removed. The global assessment from the surgeon on the joint healing will be documented as: not assessable, not healed, partially healed, or healed.

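### Fracture union and stable AC joint healing are given the full analysis population as denominator, which includes patients in whom the outcome cannot occur or is never assessed

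*Protocol article*

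**What the plan says.** Section 2.4.2 of the protocol article names three rates in one sentence: reoperation due to adverse device effects, fracture union, and stable AC joint healing. For all three it sets one denominator: "fracture union rate, rate of stable AC joint healing at one-year post-removal, the full analysis population will be used as the denominator". The same section uses this population for adverse event rates, irrespective of dropout.

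Other parts of the article describe who can have these outcomes:

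- Section 2.3.1: hook plates are "used for fixation of lateral clavicle fractures and dislocations of the acromioclavicular joint". Section 2.4.1 plans the study around "a minimum of 30 patients with shaft fractures treated with Clavicle Plates and 30 patients with lateral fractures/AC dislocations treated with Clavicle Hook Plates".
- Section 2.3.7.2 lists the AC outcome with a limit: "Rate of stable AC joint healing (if applicable) at one-year post-removal, clinically assessed".
- Section 2.3.7.3 restricts AC assessment to hook-plate patients and adds that "the AC joint healing status will be assessed only after the plate has been removed".
- Table 2 (Clavicle Plates) has no joint-healing row. Table 3 (hook plates) has joint healing only at the post-removal visits, and marks bone healing as recorded only where applicable.

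Section 2.4.2 leaves the definition of the analysis populations to the SAP. It also says that missing data will be handled endpoint by endpoint.

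**The concern.** A rate describes a device only if everyone in the denominator could have had the outcome and could have been observed to have it. Reoperation meets that test, since any implanted patient can be reoperated. Union does not, because a patient with a pure AC dislocation has no fracture. AC healing does not either, because a retained hook plate means no assessment, and Clavicle Plate patients are never assessed for it.

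The article does not call these patients failures. The effect is arithmetical: someone who counts below the line and can never count above it lowers the rate exactly as a failure does.

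Union and AC healing are two of the five clinical-performance outcomes in section 2.3.7.2. The study has no hypothesis test, so these percentages are its results, and the Discussion offers them as a basis for future comparative studies. Under the literal rule, the hook-group union rate would largely reflect how many AC dislocations were enrolled.

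**Working it through.** **Planned numbers.** Section 2.4.1 wants 30 patients per group and assumes 20% dropout at two years. 30 / (1 − 0.20) = 37.5, rounded up to 38 per group, and 2 × 38 = 76. This reproduces the plan's figure.

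**Assumption.** Let s be the share of the hook group with a pure AC dislocation. The article gives no value. I take s = 50%, with a range of 25–75%. To isolate case mix, suppose nobody drops out and every fracture unites.

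**Union.** Patients without a fracture = 38 × s. The caps are:

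- hook group: (38 − 38s) / 38
- pooled: (76 − 38s) / 76

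| s | No fracture | Hook-group cap | Pooled cap |
|---|---|---|---|
| 25% | 9.5, taken as 10 | 28/38 = 73.7% | 66/76 = 86.8% |
| 50% | 19 | 19/38 = 50.0% | 57/76 = 75.0% |
| 75% | 28.5, taken as 28 | 10/38 = 26.3% | 48/76 = 63.2% |

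Without rounding to whole patients, the hook-group cap is 1 − s, that is 75%, 50% and 25%. In every row the rate among patients who had a fracture is 100%. At s = 50% the pooled 57/76 has a Clopper-Pearson 95% interval of 63.7–84.2%, which excludes that 100%.

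**AC joint healing, pooled.** Only the 38 hook-plate patients can be assessed. With every plate removed, every patient followed and every joint healed, the rate is 38/76 = 50.0% (95% interval 38.3–61.7%). This cap needs no assumption about s.

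**AC joint healing, by device.** Clavicle Plate patients leave the calculation. With r retained plates the cap is (38 − r)/38. The article gives no figure for r. Section 2.3.4.5 limits follow-up to two years from implantation, so a plate removed much later than 12 months (24 − 12) also leaves no room for the one-year post-removal visit.

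**Can the population definition absorb this?** Adverse event and reoperation rates use the same full analysis population, and they need patients with pure AC dislocations in it. One population cannot both contain and exclude them, so the SAP could correct the union rate only by departing from this sentence.

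**The case against.** The strongest reply is that section 2.4.2 is a condensed sentence to be read with the rest. Table 3 marks bone healing as conditional, section 2.3.7.2 does the same for the AC outcome, and section 2.3.7.3 limits AC assessment to hook plates. The populations and missing-data rules are deferred to the SAP. The study is descriptive, and every bone-healing category will be tabulated. This shows that a restriction was probably intended. It does not remove the conflict, because the one sentence that fixes the denominator omits the restriction.

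Other parts of the reply stand, and they limit the point:

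- **Dropout.** A reader might multiply the caps by 0.8 and conclude that the hook-group union rate cannot exceed about 40% (15/38 = 39.5%). The documents do not support that. Bone healing is recorded from 6 weeks onward, the 20% dropout is at two years, section 2.3.6 allows use of data collected before termination, and the article ties the union rate to no time point. A patient who healed and was lost later can still count as united.
- **Opposite handling of dropouts.** A reader might also infer that the rule treats a dropout as event-free for reoperation and as unhealed for union. Missing data are left to the SAP by endpoint, and a sensitivity analysis excluding dropouts without an adverse event is named, so this is not established.
- **Lateral fracture with an intact AC joint.** Table 3 schedules joint healing for the whole hook group, so such a patient may be scored as healed. The documents do not show that these patients lower the AC rate.
- **Retained plates.** Table 3 shows removal surgery as a scheduled visit, so retention may be uncommon. The defect is certain in kind, but its size is unknown.

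**Conclusion.** The point holds. Read literally, section 2.4.2 keeps patients with pure AC dislocations in the union denominator and retained hook plates in the AC denominator. If the AC rate is pooled, all Clavicle Plate patients are in its denominator too. This conflicts with the limits in section 2.3.7.2 and Table 3.

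On an assumed 50% share of pure AC dislocations (range 25–75%), case mix alone caps the hook-group union rate at 50% (about 75% down to 25%) and the pooled rate at 75% (about 87% down to 63%). A pooled AC rate cannot exceed 50% whatever the share. The article does not say whether these rates are pooled or by device. The no-fracture and retained-plate problems exist either way, while the Clavicle Plate problem arises only if the AC rate is pooled. Dropout may lower the figures further, but by how much depends on when healing was recorded and on the SAP's missing-data rule, so no cap that includes dropout should be quoted.

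**What to change.** Rewrite the sentence in section 2.4.2, and carry the change into the SAP before any analysis is run:

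- **Reoperation:** keep the full analysis population.
- **Union:** patients in that population with a clavicle fracture.
- **Stable AC joint healing:** hook-plate patients for whom the outcome applies and whose plate was removed. State who counts as applicable, since the article leaves open whether lateral fractures do.
- **Reporting:** give each rate by device group, with the numbers not applicable, not removed and not assessed.
- **Missing outcomes:** show the rate among assessed patients, and again with missing counted as not healed, both tied to the same at-risk group. Neither is free of bias alone: complete cases can flatter the device, and missing-as-unhealed can penalise it.

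Injury type (section 2.3.4.2) and removal date (section 2.3.7.7) are already collected, so no new data are needed. The cost is precision. For example, 19 of 19 united gives a 95% interval of 82.4–100%, against 90.7–100% for 38 of 38. The wider interval is the correct one for the patients at risk.
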